#### Other Data Acquisition

We will aim to collect demographic data, including information about protected characteristics (eg, age, gender, ethnicity, pregnancy, marital status, highest qualification, religion, sexual orientation, disability, first language, caring responsibilities, and refugee and asylum seeker status). We will also gather job-related information on the job sector, job title, duration in the post, monthly salary, presenteeism, absenteeism, turnover intention, and service use (including well-being programs, primary care, outpatient appointments, inpatient appointments, private therapy, and medication), and, where available, practitioner or facilitator feedback data. Furthermore, data will be collected on recruitment uptake or rate; session attendance; compliance with treatment; any adverse events (AEs); attrition or dropout rates (in between intervention and loss to follow-up); and reasons for attrition or noncompliance, including diversion and inclusion barriers to intervention uptake and implementation.

#### Qualitative Study

A subsample of 30 participants (n=15, 50% in each intervention arm) will be recruited for the qualitative study after 20-week randomization (within an 8-week data collection window). The semistructured interviews will inquire into participants’ perceived changes after intervention and their experience and views in relation to intervention uptake and acceptability. They will be conducted online via Microsoft Teams and will be video or audio recorded for transcription purposes, depending on the participant’s preference for keeping the camera on or using the audio only.

#### Qualitative Study Outcomes

Semistructured interview data will elicit the following qualitative outcomes from participants:

Perceived changes in their well-being and quality of life (ie, beneficial impacts and adverse effects)Perceived changes in their levels of work satisfaction, engagement, and performance (ie, beneficial impacts and adverse effects)Nature of well-being support sought and whether the given intervention has met their expectationsBarriers and drivers to intervention route to uptake, attendance, engagement, and adherence (including aspects related to the intervention delivery and content or structure, personal or work circumstances, and managerial support)Recommendations for future improvement of intervention design and implementation

### Dissemination

We will report the trial findings and recommendations on the digital intervention product refinements to our PPIE group and other stakeholders, scientific audiences, the NHS confederation, NICE, networks of nursing and medical directors of NHS organizations, social care directors, Academic Health Science Network-East Midlands, NHS England (previously known as Health Education England), and professional well-being practitioner groups who will be required to staff and deliver these interventions.

### AEs in the Study

The structured context of MBCT-L and SRP includes psychoeducational materials or resources on how to manage distressing experiences arising during meditation or at other times in practice. The trained practitioners or facilitators delivering these interventions have a mechanism in place as routine practice for providing tailored advice and support at any stage. Once participants have commenced the intervention, they are prompted to report any AEs, emotional or physical, to the practitioner or facilitator. This will trigger a consultation meeting between the participant and the therapist team, who will provide advice and refer the participant to further support as appropriate (within the mental health well-being team, general practice, or mental health services). Participants are prompted to make adjustments during the meditation exercises to reduce any bodily discomfort and exert physical effort at a level that is comfortable for them during any body-moving exercises. Participants are also signposted in the PIS to available well-being support resources that they can access outside the trial.

AEs may occur and may or may not be linked to the intervention. These can include exacerbated emotional reactions, an increase in frequency or intensity of a preexisting (mental or physical) episodic event or illness, and worsening of symptoms present at baseline following the start of the study. Any AEs will be assessed for seriousness, expectedness, and causality. The causal relationship of an AE to the study intervention is assessed by the chief investigator in consultation with medical experts of the research team as “possible,” “probable,” or “definite” and will be reported as an AE in the study log and the ARC-EM Scientific Committee. Participants will be asked to contact the practitioner leading their intervention group or the study site immediately in the event of an AE. Any AEs will be recorded and closely monitored until resolution, stabilization, or it has been shown that the study treatment or intervention is not the cause. The chief investigator shall be informed immediately of any AEs and shall determine the seriousness and causality in conjunction with the therapists and the medical practitioners who are part of the research team. These will be recorded in the study log and instigate further investigation and follow-up if or as appropriate. The chief investigator shall be responsible for all AEs reported to the ARC-EM Scientific Committee and Ethics Committee Board.

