#### The MBCT-L Intervention

MBCT-L integrates conventional cognitive therapy techniques with stress reduction techniques and mindfulness practice, as in the original MBCT version, but has been adapted to apply to the general population as per established protocol [9]. The program includes 8 online weekly sessions lasting approximately 2 hours and an online practice day lasting approximately 6 hours. MBCT-L will run for 9 consecutive weeks or 10 weeks if a 1-week break is included (eg, due to school break or holidays) in a group-based format with an average of 8 participants recruited per group. The content includes themed teaching every week and guided meditation practices (eg, breathing practice and body scan), as well as everyday homework practices lasting 30 to 45 minutes. Participants will receive frequent automated text reminders about their upcoming sessions and homework or home practices via an automated text messaging service provided by a Generated Health system, Florence [27]. The program will be delivered by approximately 8 trained MBCT practitioners or facilitators across the main NHS trust sites, who are part of the teaching team involved in the MBCT-L interventions already being offered to public sector staff through the NHS trust services and have been trained under, and follow, the same MBCT training protocol [9].

The MBCT-L program broadly follows an overarching structure of developing mindfulness skills intended to enhance attentional control and awareness, cultivating a deeper understanding of how distress is created and maintained and how mindfulness training can address factors that contribute to its maintenance, learning skillful ways of relating to experience developed through awareness and practice, and learning to recognize unhelpful reactive patterns in everyday life and cultivate the capacity to respond to these with mindfulness and compassion. In the second part of the program, participants practice the application of this learning to everyday life, including work, to respond more effectively to stress and enjoy the positive aspects of life.

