#### The SRP Intervention

The SRP intervention will be delivered in 4 online weekly sessions lasting approximately 2 hours and running for 4 consecutive weeks or 5 weeks if there is a 1-week break (eg, school break or other holidays). The program will run as it is currently being offered as standard care across Nottinghamshire and all the other regions in England, through NHS Talking Therapies (formerly known as Improving Access to Psychological Therapies) or NHS trust or other health care services. Its content is focused on psychoeducation around well-being and stress management, combined with relaxation strategies [23]. Specifically, the program consists of sessions focused on areas of stress, well-being, and goal setting; sleep hygiene; anxiety and depression; behavioral activation; problem-solving; thinking errors; and a final recap, review of goals and thoughts for future well-being. Participants will be encouraged to work between sessions by engaging in a stress reduction technique of their preference daily for approximately 30 minutes and through a diary activity (eg, behavioral activation diary). They will receive email reminders to complete these and attend the upcoming sessions.

Recognizing that SRP programs can vary in their content and format or structure in how they are being offered across NHS trusts and other organizations in the United Kingdom, the standard 4-session structure will be adopted as the optimized form of its delivery. The SRP will also explicitly avoid embedding any mindfulness-based techniques, as these are not core or essential elements of a stress reduction approach, while it is important for the RCT to adhere to NICE-recommended standards, which indicate that 4 sessions are optimal when group sessions are delivered by experienced facilitators. The program will be delivered by 3 experienced facilitators (2 psychological well-being practitioners and 1 psychiatrist) across the SRP groups recruited across all sites, ensuring consistent delivery of the intervention across all participating NHS sites.

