### Outcome Assessments

#### Overview

Participants who provide consent will be required to complete the outcome assessments via web-based surveys through REDCap, which will contain the primary and secondary measures at baseline (before the intervention); up to 2 weeks before randomization; and at follow-up time points at weeks 6, 12, and 20 after randomization. Participants in both arms will receive the same outcome measures. Participants will be able to save their responses and return to the survey to complete their assessments at a later point. For both incomplete baseline and follow-up surveys, participants will receive 3 automated email reminders through REDCap asking them to complete the survey. If the survey is still incomplete, the research team may then send out 1 further personalized email reminder from the study email address.

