Possible unintended outcomes might include adverse effects following engagement with the interventions. Currently, relatively little has been reported on the potential adverse effects of MBCT in nonclinical populations. However, in a recent systematic review of AEs in meditation practices and meditation-based therapies, including relaxation and MBCT exercises [48], it was found that adverse effects during or after meditation practices occurred in nonclinical populations too and were associated with meditation practices, particularly anxiety and depression. The overall prevalence of meditation AEs was 8.3% in 55 studies, reporting at least 1 adverse effect, and this percentage is similar to those reported for psychotherapy practice in general. The structured context of MBCT and SRP includes psychoeducational materials and resources on how to manage distressing experiences arising during meditation or at other times, while there is a mechanism in place in the trial for the participant to consult the therapist in the event of excessive discomfort or distress or to be directed to other well-being support. This trial will log any adverse effects reported during the intervention period and at follow-up, with plans in place to review these events and the conduct of the trial with the National Institute of Health and Care Research ARC-EM Scientific Committee and the external steering committee as well as to terminate a participant’s engagement in the trial or the trial itself, should the criteria for doing so be fulfilled.

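### Adverse-event prompting runs through facilitators, whose contact lasts about twice as long in MBCT-L as in SRP, so raw adverse-event counts by arm are open to ascertainment bias

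*Protocol article*

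**What the plan says.** The procedure is in the protocol article under AEs in the Study. Prompting begins with the programme and is directed to the person delivering it: "Once participants have commenced the intervention, they are prompted to report any AEs, emotional or physical, to the practitioner or facilitator". The same section adds a self-initiated route with no end date: "Participants will be asked to contact the practitioner leading their intervention group or the study site immediately in the event of an AE".

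Other sections bear on the window:

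- Anticipated Findings (Discussion): "This trial will log any adverse effects reported during the intervention period and at follow-up". No method of eliciting events at follow-up is given.
- Other Data Acquisition lists AEs among the data to be collected ("session attendance; compliance with treatment; any adverse events (AEs); attrition or dropout rates (in between intervention and loss to follow-up"), without an instrument or time point.
- Outcome Assessments, Overview describes the online surveys at baseline and at weeks 6, 12 and 20 as instruments "which will contain the primary and secondary measures at baseline" and at follow-up. An AE item is not mentioned.
- Qualitative Study Outcomes includes adverse effects among the interview topics, for 30 participants after week 20.

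The programmes differ in length. For MBCT-L, "The program includes 8 online weekly sessions lasting approximately 2 hours and an online practice day lasting approximately 6 hours", and "MBCT-L will run for 9 consecutive weeks or 10 weeks if a 1-week break is included". SRP has four sessions of about 2 hours, "running for 4 consecutive weeks or 5 weeks if there is a 1-week break".

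**The concern.** A count of AEs by arm reflects how often events happen and how often someone asks about them. Here the asking is tied to treatment contact, and treatment contact differs by design. With equal true harm, the longer programme would tend to show more recorded events.

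The article's own account of AEs reaches beyond the session weeks. It counts worsening of baseline symptoms after the study starts, and the Discussion notes that adverse effects can arise after meditation practice as well as during it. People who leave the programme, or who may not continue after missing the first sessions, can remain in the trial but lose the facilitator's prompt.

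The counts will be used. The monitoring committee reviews safety data, the Discussion links review of these events to possible termination of a participant's engagement or of the trial, and the results are meant to guide which programme is commissioned. A contact-time artefact could be read as excess harm from MBCT-L.

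**Working it through.** The article gives no figure for AE ascertainment, so there is none to reproduce. The check takes the programme lengths and asks what they do to recorded counts under stated assumptions.

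**Inputs**

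- MBCT-L contact: 9 weeks, or 10 with a break; 8 × 2 h + 6 h = 22 h (The MBCT-L Intervention).
- SRP contact: 4 weeks, or 5 with a break; 4 × 2 h = 8 h (The SRP Intervention).
- Follow-up: 20 weeks from randomization.
- Sample: 260 at 1:1, so 130 per arm (Sample Size).
- Illustrative 20-week risk: 8.3% in both arms. This borrows the prevalence of meditation AEs cited in the Discussion; using it as a common 20-week risk is an assumption.
- c: the fraction of events outside facilitator contact that still get recorded. The article does not give it.

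**Step 1: contact.** Weeks: 9/4 = 2.25 or 10/5 = 2.0. If a break falls in one arm only, 9/5 = 1.8 or 10/4 = 2.5. Share of 20 weeks: 45–50% in MBCT-L, 20–25% in SRP. Hours: 22/8 = 2.75.

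**Step 2: spurious ratio.** Assume equal true risk, events spread evenly over 20 weeks, full recording during w weeks of contact and a fraction c otherwise. The recorded share is [w + c(20 − w)]/20, and the MBCT-L:SRP ratio is

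[w₁ + c(20 − w₁)] / [w₂ + c(20 − w₂)].

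Expected people with an event: 0.083 × 130 = 10.8 per arm, multiplied by the recorded share.

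| c | 9 v 4 weeks | 10 v 5 weeks | Recorded per 130, 9 v 4 | Recorded per 130, 10 v 5 |
|---|---|---|---|---|
| 0 | 9/4 = 2.25 | 10/5 = 2.00 | 4.9 v 2.2 | 5.4 v 2.7 |
| 0.25 | 11.75/8 = 1.47 | 12.5/8.75 = 1.43 | 6.3 v 4.3 | 6.7 v 4.7 |
| 0.5 | 14.5/12 = 1.21 | 15/12.5 = 1.20 | 7.8 v 6.5 | 8.1 v 6.7 |
| 1 | 1.00 | 1.00 | 10.8 v 10.8 | 10.8 v 10.8 |

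**Step 3: sensitivity.** The assumed risk cancels from the ratio. A constant-hazard version with 20-week risks of 5%, 8.3% and 15% gives 1.96 to 2.24 at c = 0, 1.43 to 1.47 at c = 0.25 and 1.20 to 1.21 at c = 0.5.

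**Step 4: which c applies.** Reports to the study site and the promised logging at follow-up both put c above zero. Neither is described as a prompt applied in the same way to both arms, so nothing in the article supports c = 1 either. The interviews reach 30/260 = 11.5% of participants and do not settle it.

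**The case against.** The strongest reply is that AE recording is not confined to facilitator contact. A reader might infer from the AE section that events are captured only while sessions run, and that the harms comparison is therefore biased. The article does not support that reading. The study-site route has no end date, logging at follow-up is stated, and the interviews ask about adverse effects. Those points stand, and they make c = 0 a worst case rather than an estimate.

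Second, the description of the surveys is not a full list. The economic section adds a quality-of-life measure and a service-use inventory at the same time points, and the Discussion says that further data are collected through the web-based survey. An AE item may sit in the full protocol, which is not shown. That stands too: silence in a condensed article is not proof of absence.

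Third, no between-arm test of AEs is stated, and AEs are not a listed outcome. Symptom scales for stress, anxiety, depression and trauma are collected identically in both arms, so symmetric information on worsening exists. This limits the point to descriptive AE counts, but the scales do not replace an AE log.

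Fourth, the 8.3% concerns meditation, whereas SRP avoids mindfulness techniques, and events may cluster around sessions and practice. The even-spread model is only an illustration. If events do cluster, part of an MBCT-L excess could be real harm from a longer programme. Contact-linked counts could not separate that from ascertainment.

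What none of this removes is that the one active prompt described lasts about twice as long in one arm.

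**Conclusion.** The point holds as a risk of ascertainment bias in raw AE counts by arm, not as a demonstrated bias. Prompted contact is 2.0 to 2.25 times as long in MBCT-L with matched breaks. Under equal, evenly spread true risk, the spurious ratio runs from that figure with no capture outside contact, through 1.4 to 1.5 at 25% and 1.2 at 50%, to 1.0 at full capture. In this model the direction is always towards more recorded events in MBCT-L unless capture outside contact is as complete as during it. The true position in that range is unknown because the article does not give the capture rate. If the surveys carried a common AE question, most of the concern falls away and the article need only say so.

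**What to change.** The sound method is one identical question in the 6-, 12- and 20-week surveys in both arms, including people who left the programme, asking about any new or worsened emotional or physical problem since the last survey and its onset date. That solicited record should be the basis of any between-arm harms summary, with facilitator reports listed separately. At the design stage this costs one or two survey items and some extra minor events to classify.

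The Results section says that follow-up data collection finished on September 30, 2024, so the item cannot be added now. Two cases remain:

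- **If such an item was used:** describe it and base the by-arm summary on it.
- **If not:** report all AEs by arm with time of onset and source (facilitator, study site, other). Add a summary restricted to the session window common to both arms, about the first 4 weeks. State that later facilitator-reported counts are not comparable between arms.

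The second option needs no new data where onset and source were logged. Its price is few events: at the assumed 8.3%, 10.8 × 4/20 is about 2.2 people per arm. It also leaves out harms that arise later in the longer programme, so the full listing must be kept beside it.

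### The stated AE causality scale has no level for an unrelated event, although the same section expects some AEs to be unrelated

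*Protocol article*

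**What the plan says.** All the relevant rules are in the protocol article, mostly under AEs in the Study.

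- Unrelated events are expected: "AEs may occur and may or may not be linked to the intervention".
- The assessment covers every event: "Any AEs will be assessed for seriousness, expectedness, and causality".
- The causality levels are named once. The relationship "is assessed by the chief investigator in consultation with medical experts of the research team as “possible,” “probable,” or “definite". The same sentence then sends the event, as an AE, to the study log and to the ARC-EM Scientific Committee.
- Any AE is to be recorded and followed until it resolves, stabilises, or "it has been shown that the study treatment or intervention is not the cause".
- A later sentence says the chief investigator "shall determine the seriousness and causality in conjunction with the therapists and the medical practitioners who are part of the research team". It names no levels.

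Elsewhere, Other Data Acquisition lists AEs among the data to be collected, and Anticipated Findings says "This trial will log any adverse effects reported during the intervention period and at follow-up". Under Ethical Considerations, the ARC-EM Scientific Committee serves as both steering and data monitoring committee and reviews safety data.

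**The concern.** A causality scale is useful only if it separates events that the intervention may have caused from those it did not. Here the lowest level listed is already *possible*. An assessor who follows the sentence as written has nowhere to put a clearly coincidental event, such as a viral illness, except among the related ones.

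What is at stake is how the trial's safety information is interpreted. Anticipated Findings notes that relatively little has been reported on adverse effects of MBCT in nonclinical populations, so attribution is part of what this trial could add. If *possible* can mean either a real suspicion or merely the lowest available box, neither the committee nor a reader of the results can tell which was meant.

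**Working it through.** No arithmetic beyond a count of levels applies, so the check sets the sentences of AEs in the Study side by side.

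1. **Which events are rated?** All of them. The sentence on seriousness, expectedness and causality covers any AE.
2. **Which ratings are available?** Three: *possible*, *probable* and *definite*. Levels implying at least possible relatedness: 3. Levels for unlikely or unrelated: 0.
3. **Which conclusions does the section expect?** Both. Its opening sentence allows for AEs not linked to the intervention, and its monitoring rule allows a finding that the intervention is not the cause.
4. **Can the scale record both?** No. Steps 1 and 3 together require a rating for an unrelated event, and step 2 provides none.

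The rating sentence can be read in two ways.

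- **As the full scale.** Every assessed AE is then at least possibly related by construction. The related events are simply all the events, and the attribution carries no information beyond the grading within the related levels.
- **As the levels that lead to reporting.** The sentence joins the rating to reporting as an AE in the study log and to the committee, so it could mean that only events at these levels are reported. An unrelated event would then go unreported. That conflicts with the commitment in the same section to record any AE, with its later statement that AEs go into the study log, and with the promise in Anticipated Findings to log any adverse effects.

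Neither reading agrees with the rest of the section. The later sentence on determining causality does not settle the matter, because it supplies no levels.

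**The case against.** The strongest reply is that the section does provide for an unrelated conclusion, because it says that the intervention may be shown not to be the cause. The three words might then name only the degrees of relatedness, with an unlisted unrelated outcome beside them. The article also condenses a full protocol and an AE form that are not shown, either of which may hold a complete scale.

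Part of this stands. It would be too strong to say that the trial has no means of calling an AE unrelated; what can be said is that the stated scale offers no such rating. The condensation argument does not remove the point. The article does not leave the scale to another document: it states one, and that scale conflicts with its neighbouring sentences. A fuller scale elsewhere would still leave this text to be corrected.

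A reader might also infer four stronger conclusions, which the article does not support.

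- **That a planned count of related AEs is wrong.** The article defines no count, rate or between-arm comparison of related AEs. Distortion would follow only if the three levels were used literally and related events were then tabulated.
- **That unrelated AEs are missing from the log.** The sections cited above commit to collecting, recording and logging any AE. The reporting reading creates a conflict with those commitments; it does not show that events were lost.
- **That the committee's termination decisions rest on a faulty figure.** Anticipated Findings refers to criteria for ending a participant's engagement or the trial but does not give them. Nothing ties them to causality ratings.
- **That the scale biases the comparison against MBCT-L.** MBCT-L runs for 9 or 10 weeks and SRP for 4 or 5, so the opportunity to report events to a facilitator differs. That would hold under any causality scale, and an added level would not remove it. It is a separate question of ascertainment.

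**Conclusion.** The point holds as an internal contradiction in the safety section. Every AE must be rated for causality, the scale as stated has three related levels and none for unrelated, and the same section expects some events to be unrelated. Followed literally, the rule classes every assessed AE as at least possibly related, which would make any reported attribution uninformative.

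This rests on the wording of the article alone. It assumes nothing about how many AEs occurred or how they were actually rated, and the article gives no basis for estimating either. If the form in use already had an unrelated option, only the text needs correcting. The primary outcome, its analysis and the sample size are unaffected.

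**What to change.** 1. Add a *not related* level, or a combined *unlikely/not related* level, to the causality scale, so that it matches the section's own statements that AEs may be unlinked and that the intervention may be shown not to be the cause. A longer scale is a matter of convention and is not needed to resolve the contradiction.
2. Separate rating from reporting: say that logging and reporting to the ARC-EM Scientific Committee apply to every AE whatever its rating.
3. State which rule was used during the trial. Before reporting, check the logged events and re-rate any that were placed in *possible* only for want of a lower category. Re-rating reaches only events that were logged. If the rating sentence was used as a filter, say so when the safety results are reported.

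The cost is a sentence or two of text, one option on the form if it is not already there, and a review of the logged events. According to Results, follow-up data collection finished on September 30, 2024, so the work is confined to the log and needs no new participants, procedures or data collection.

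### The article gives two different rules for who judges adverse-event causality, and one of them gives therapists who know the allocation, from teams described separately by arm, a share in rating seriousness and cause

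*Protocol article*

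**What the plan says.** The section AEs in the Study contains two statements about who judges an adverse event.

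- First statement: causality "is assessed by the chief investigator in consultation with medical experts of the research team", graded as possible, probable or definite. Therapists are not mentioned.
- Second statement, later in the same paragraph: the chief investigator "shall determine the seriousness and causality in conjunction with the therapists and the medical practitioners who are part of the research team". Therapists are now included, and seriousness is covered as well as causality.

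Therapists are also the main point of intake. Once the intervention has begun, participants are told that "they are prompted to report any AEs, emotional or physical, to the practitioner or facilitator", and the report leads to a meeting with the therapist team. The same section also asks participants to "contact the practitioner leading their intervention group or the study site immediately in the event of an AE".

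The delivery staff are described arm by arm. For MBCT-L, "The program will be delivered by approximately 8 trained MBCT practitioners or facilitators across the main NHS trust sites". For SRP there are 3 facilitators, one of them a psychiatrist.

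The section Randomization and Blinding covers the researchers who assess outcomes and the study statistician. The section Ethical Considerations gives an independent committee the task of reviewing safety data.

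**The concern.** Whether an event was serious, and whether the programme caused it, are matters of judgement. Judgements made with knowledge of the arm can drift, and can drift differently in the two arms if different people feed into them. The second rule brings in therapists who know which programme the participant received, because they deliver one of them. If the MBCT-L and SRP teams have different thresholds for calling an event related or serious, a tabulation by judged relatedness would mix that difference with any difference in harm.

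The Discussion says relatively little has been reported on adverse effects of MBCT in nonclinical populations. It also says logged events feed into review of the conduct of the trial, including possible termination. Readers are therefore likely to use the ratings, and the rule that produced them should be stated once and clearly.

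**Working it through.** The plan gives no figure on this point to reproduce. The check is a comparison of the sections, followed by an illustration whose rating shares are assumptions.

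**1. Do the two statements agree?** The decision-maker is the chief investigator in both. The medical experts in the first and the medical practitioners in the second may well be the same people. The remaining difference is that therapists appear only in the second. So the conflict is about causality, where one rule excludes therapists and the other includes them. For seriousness, only the second statement names anyone, and it includes therapists.

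**2. Which raters are common to both arms?** The chief investigator and the research-team medical practitioners are. Only the therapist contribution can differ by arm, because the Interventions section describes two sets of delivery staff.

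**3. Are the raters blinded?** Therapists cannot be. For the chief investigator and the medical practitioners, blinding when rating events is not stated. The Data Management Plan keeps randomization data from researchers to protect blinding, but discussing an event with a therapist who delivers one programme would tend to reveal the arm.

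**4. Is there a later safeguard?** The independent committee reviews safety data, and events are reported to it and to the ethics committee. Neither is described as rating causality again, masked or otherwise.

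**5. Are the medical raters separate from delivery?** The article does not say. One SRP facilitator is a psychiatrist, so the question is a practical one.

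**6. Illustration of scale.** From the documents: 260 randomized 1:1, so 130 per arm, and the 8.3% meditation adverse-event prevalence cited in the Discussion. Assumed: 8.3% applies equally to both arms, each event is a different person, and the share rated as related is as shown.

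Expected events per arm = 0.083 × 130 = 10.8.

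| Share rated related (one arm, other arm) | Related events | Ratio |
|---|---|---|
| 50%, 50% | 5.4, 5.4 | 1.0 |
| 50%, 75% | 5.4, 8.1 | 0.67 |
| 25%, 75% | 2.7, 8.1 | 0.33 |

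True harm is identical in every row. For the most extreme row the proportions are 0.083 × 0.25 = 0.0208 and 0.083 × 0.75 = 0.0623. The difference is 0.0415, with standard error √(0.0208 × 0.9792/130 + 0.0623 × 0.9377/130) = 0.0246, giving z ≈ 1.7 (ignoring clustering). Differential rating can thus change how a descriptive table looks, but at these counts even the extreme case stays below 1.96.

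**The case against.** The strongest reply is that this is a small wording discrepancy. One person, the chief investigator, decides in both arms with the same medical colleagues. Therapists hold the clinical information, so consulting them is reasonable. The phrase about belonging to the research team can be read as qualifying the therapists too, in which case it means study-team therapists and not the facilitator of the participant's group; the Discussion does mention a lead therapist team. All adverse events are to be recorded whatever their cause, so a count of all events by arm does not depend on the causality rating. An independent committee sees the safety data. Follow-up data collection ended on September 30, 2024, so new wording cannot change how events were collected.

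Much of this stands, and it rules out a stronger reading. A reader might infer that related events are rated by wholly different, unblinded and interested people in each arm. The documents do not support that. The main raters are common to both arms, the text does not expressly say that the treating therapist takes part, and a stake in the answer is an inference. A reader might also infer that the causality rating, through therapist opinion, decides how long an event is watched. The section lets monitoring end when the intervention is shown not to be the cause, but does not tie that showing to therapists.

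What the reply does not remove is that the two statements disagree, that therapists who know the arm contribute under one of them, and that no masked or independent rating is described.

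**Conclusion.** The point holds in a limited form. The article states the causality rule in two ways that must be reconciled. Under the second, therapists who know the allocation and whose delivery teams are described separately by arm contribute to seriousness and causality ratings. The other raters are common to both arms, and their blinding at that step is not stated. Ratings may therefore differ by arm for reasons other than harm.

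The size of this cannot be derived from the documents. The figures in the illustration rest on assumed rating shares and on applying a meditation-related prevalence to SRP, which is designed to avoid mindfulness techniques; they show possibility only. It would also go too far to call a comparison of related events the trial's harms result, since the article names no such comparison as an outcome. The primary analysis is untouched. This is an inexpensive improvement to the handling of harms.

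**What to change.** Replace the two statements in AEs in the Study with one:

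- Therapists provide the facts of the event in writing.
- The chief investigator, with research-team medical practitioners who deliver neither programme, rates seriousness and causality.
- The rating is made from a narrative with programme name and session content masked where feasible.

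Because data collection is complete, the practical step is to re-rate the events already in the study log in this way before the harms table is produced, and to state in the report which panel was used. Report all adverse events by arm regardless of judged relatedness, alongside any table by relatedness, so that readers have a count that does not depend on the rating.

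The cost is a wording change and a re-rating by staff already on the team, with no new data needed. The therapist's opinion on cause is lost, though not the therapist's account. Masking will sometimes fail, for example when an event arose during meditation; such cases should be noted.
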